## Summary

|                            |                                                                                                                                                                                                                                                                                                                                                                                                                                                                                       |
|----------------------------|---------------------------------------------------------------------------------------------------------------------------------------------------------------------------------------------------------------------------------------------------------------------------------------------------------------------------------------------------------------------------------------------------------------------------------------------------------------------------------------|
| Title               | 
Surveillance of family carers with close contact to persons from risk groups in the Magdeburg area in the SARS-CoV-2 pandemic
 
Acronym: SuRIP - SARS-CoV-2
 
A prospective, longitudinal, regional cohort study to develop surveillance concepts and to test their acceptance among carers/relatives within the framework of the nationwide research network on applied surveillance and testing (B-FAST).
                                                          |
| Study population    | 
Relatives caring for persons from risk groups (vulnerable groups), such as senior citizens or persons with disabilities
                                                                                                                                                                                                                                                                                                                                                        |
| Primary objective   | 
Practicability and acceptance of different test frequencies of a simple, self-performable and self-evaluable test system (saliva test) among caring relatives.
                                                                                                                                                                                                                                                                                                                 |
| Secondary objective | 
Obtaining data for modelling the test frequency.
 
Verification of the test quality (sensitivity and specificity) of self-test systems.
 
Investigate the influence of external contacts of the carers (e.g. occupational) and the current incidence of infection and the associated potential risks of transmission of SARS-CoV-2 to the person being cared for.
 
Measurement of vaccination acceptance and willingness to vaccinate in this group of people.
 |

|                             |                                                                                                                                                                                                                                                                                                                                                                                                                                                                                                                                                                                                                                                                                                                                                                                                                                                                                                                                                                                                                                                                                                                                                                             |
|-----------------------------|-----------------------------------------------------------------------------------------------------------------------------------------------------------------------------------------------------------------------------------------------------------------------------------------------------------------------------------------------------------------------------------------------------------------------------------------------------------------------------------------------------------------------------------------------------------------------------------------------------------------------------------------------------------------------------------------------------------------------------------------------------------------------------------------------------------------------------------------------------------------------------------------------------------------------------------------------------------------------------------------------------------------------------------------------------------------------------------------------------------------------------------------------------------------------------|
| Study design         | 
Prospective, longitudinal pilot cohort study with serial self-testing using a saliva test initially over a period of 6 weeks. 45 family caregivers are randomised into 3 groups with different test frequencies.
 
1st group: 1 time per week
 
2nd group: 2 times per week
 
3rd group: every 2 days
 
15 people will be randomly assigned to each group (lottery).
 
Recruitment: Subjects are recruited by advertisement in the local print media. Interested persons should contact the study secretariat by telephone.
                                                                                                                                                                                                                                                                                                                                                                                                                                                                                                                                                                                                                 |
| Investigation scheme | 
Visit 0: Selection of subjects according to the defined inclusion and exclusion criteria (minimum age, caring relatives, external contacts, written consents, no active COVID-19 disease; see points 2.3. and 2.4.) at first telephone contact. Randomisation of the selected subjects.
 
Visit 1: Personal visit of the subjects to the study centre, collection of a combined nasopharyngeal swab for PCR testing (exclusion of SARS-CoV-2 carrier status), blood collection for antibody determination, completion of the "first contact" and "vaccination" questionnaires by the study participants accompanied by the study staff, instructions for self-testing and documentation.
 
Visit 2-7: Weekly telephone contact (individual interviews) to query the test results, query of the "Follow up" questionnaire on the type and frequency of contacts in the last week as well as on changes in the professional and private environment, regular sending in of the salivettes for PCR testing.
 
Visit 8: Final visit, personal visit of the study participants, blood sample for antibody determination, questionnaire "final discussion".
 |
| Participating centre | University Hospital Magdeburg                                                                                                                                                                                                                                                                                                                                                                                                                                                                                                                                                                                                                                                                                                                                                                                                                                                                                                                                                                                                                                                                                                                                               |
| Funding              | Funding by the Federal Ministry of Education and Research as part of the B-FAST project of the Nationales Forschungswerk der Universitätsmedizin on Covid-19.                                                                                                                                                                                                                                                                                                                                                                                                                                                                                                                                                                                                                                                                                                                                                                                                                                                                                                                                                                                                               |

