## 2 Methods

### 2.1 Design pilot study

Prospective, longitudinal cohort study with serial self-testing with a saliva test (self-performable rapid antigen test from saliva samples) as a pilot phase over a period of 6 weeks on 45 persons. The following frequencies of self-testing will be investigated:

Group 1: 1 time per week

Group 2: 2 times per week

Group 3: every 2 days

Fifteen people are randomly assigned to each group. The allocation will be made via lots in prefabricated envelopes, which will be opened during the first visit.

The pilot phase with 45 people is to start in March 2021 (planned study period 15.03.2021 to 30.04.2021).

At the first contact (visit 1), the study design will be explained in detail to the test persons in a personal interview. They will also be informed about the blood collection and the taking of a nasopharyngeal swab for PCR testing.

After the subjects have given their written consent, the study doctor will take a blood sample to detect the presence of antibodies against SARS-CoV-2 as an indication of a previous infection and a combined throat and nasal swab to determine the SARS-CoV-2 carrier status (infection). The results will be communicated to the test persons promptly by telephone and in writing.

During this visit, the volunteers will be instructed on how to perform the saliva test, which they will carry out once on their own on site. Subsequently, the evaluation of the test is explained to the test persons. In addition, they are instructed on how to perform the saliva collection with the Salivette® system. They also carry out this test once independently on site.

In addition to the respective tests, the subjects will be given two questionnaires (questionnaire "First contact" and "Vaccinations"), which they are to complete together with the study staff at the study centre.

At the end of the first interview, each subject will be given the following materials and documents:

- corresponding number of saliva tests (depending on the randomisation group)
- appropriate number of salivettes
- written instructions for the saliva test
- form for documenting the test results (forms for documenting self-test results, Appendix 7.4.)
- stamped envelopes for the return of the salivettes
- a copy of the consent form for participation (Appendix 7.2)
- Information sheet on participation in the study (participant information, Appendix 7.1)

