### Visit schedule:

|                                                        | Visit 1
Inclusion | Visit 2
Week 1 | Visit 3
Week 2 | Visit 4
Week 3 | Visit 5
Week 4 | Visit 6
Week 5 | Visit 7
Week 6 | Visit 8
Closing |
|--------------------------------------------------------|----------------------|-------------------|-------------------|-------------------|-------------------|-------------------|-------------------|--------------------|
| Personal visit                                         | X                    |                   |                   |                   |                   |                   |                   | X                  |
| Antibody determination
Blood sample 10ml
serum   | X                    |                   |                   |                   |                   |                   |                   | X                  |
| PCR test/
nasopharyngeal swab                       | X                    |                   |                   |                   |                   |                   |                   |                    |
| Questionnaire                                          | X                    |                   |                   |                   |                   |                   |                   | X                  |
| Randomisation                                          | X                    |                   |                   |                   |                   |                   |                   |                    |
| Self-test by participants
(saliva test, salivettes) | X                    | X                 | X                 | X                 | X                 | X                 | X                 |                    |
| Query test result (by
telephone)                    |                      | X                 | X                 | X                 | X                 | X                 | X                 |                    |
| Questionnaire
(by telephone)                        |                      | X                 | X                 | X                 | X                 | X                 | X                 |                    |

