## Randomisation and pseudonymisation

[figure not shown]

Fig.1

In a lottery procedure, the test persons draw a neutral envelope containing the participant number and thus the respective group assignment (Fig. 1).

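### The Summary randomises at the Visit 0 telephone contact, but section 2.1 and the visit schedule randomise at Visit 1, where written consent is given

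*Protocol*

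**What the plan says.** The protocol dates the allocation in three places.

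- **Summary, investigation scheme.** Visit 0 covers selection against the eligibility criteria by telephone and then allocation: "Randomisation of the selected subjects". The next entry begins "Visit 1: Personal visit of the subjects to the study centre" and lists the swab, blood sample, questionnaires and self-test instruction. Randomisation is not among them.
- **Section 2.1.** "The allocation will be made via lots in prefabricated envelopes, which will be opened during the first visit". The same section fixes what the first visit is: "At the first contact (visit 1), the study design will be explained in detail to the test persons in a personal interview". Consent comes next: "After the subjects have given their written consent, the study doctor will take a blood sample".
- **Section 2.9, visit schedule.** The row "Randomisation" has a mark under Visit 1 (inclusion) and nowhere else. The table has no Visit 0 column.

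The text on randomisation and pseudonymisation describes the mechanism without naming a visit: "In a lottery procedure, the test persons draw a neutral envelope containing the participant number and thus the respective group assignment". Section 2.11.3 repeats it.

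**The concern.** A randomised comparison needs one stated moment of allocation, and that moment should follow consent. Here the Summary gives one moment, and the Methods and visit table give another.

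The order matters more than usual in this study. The three groups differ openly in burden: once a week, twice a week, or every 2 days. The primary objective is how acceptable and practicable those frequencies are. Someone who learns before the first visit that they must test every 2 days, and therefore stays away, has shown exactly the non-acceptance the study wants to measure. Because that person never consented, the refusal would appear nowhere in the data. Those left in the more demanding group would be selected for willingness, and acceptance of frequent testing would look better than it is.

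The planned analysis is descriptive (section 3) and the protocol states no adjustment for differences at entry. The comparison therefore relies on the groups differing only by chance when they start.

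**Working it through.** The protocol gives no figure on this point, so there is nothing to recalculate. The check sets the relevant texts side by side.

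| Place in the protocol | Moment of allocation | Moment of consent |
|---|---|---|
| Summary, Visit 0 | After selection at the telephone contact | Written consents named among the criteria applied at this contact |
| Summary, Visit 1 | Not listed | Not listed |
| Section 2.1 | Envelopes opened during the first visit | Visit 1, after the personal explanation and before blood and swab |
| Section 2.9, visit schedule | Visit 1 only | No row for it |
| Randomisation and pseudonymisation; section 2.11.3 | No visit named; the participant draws an envelope | Not stated |

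1. **Can both timings hold?** No. The Summary completes randomisation before Visit 1. Section 2.1 and the visit schedule carry it out during Visit 1.

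2. **Is it old text or a reading error?** The document is Version 1.0 and has no amendment log, so neither statement is superseded. The Summary sentence is complete, and so is the one in section 2.1.

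3. **Which timing fits the mechanism?** The participant personally draws a physical envelope that holds the number and the group. That fits a visit to the study centre and does not fit a telephone call. This is indirect support for Visit 1, since that text names no visit. The explicit dating comes from section 2.1 and the visit schedule. Fig. 1 is not shown and is not relied on.

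4. **Does the Summary's timing precede consent?** Read together with section 2.1, yes. The Summary names written consents among the Visit 0 criteria, but the contact is by telephone. Section 2.1 has the study explained in person and consent given at Visit 1. The protocol text describes no return of signed forms before that visit.

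5. **Would refusals before consent be counted?** No rule in the protocol captures them. Follow-up recruitment applies to subjects who leave the study during the first week. Section 2.5 keeps the data of people who withdraw a consent already given. Someone who never attends Visit 1 falls under neither rule.

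6. **What must happen for bias to arise?** Three things together: allocation before Visit 1, disclosure of the group before Visit 1, and attendance that depends on the group. If the envelope stays closed until Visit 1, the second condition fails.

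7. **Does section 2.1 settle the order within Visit 1?** Not explicitly. It places consent before the blood sample and swab, but does not say whether the envelope is opened before or after consent.

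**The case against.** The strongest reply is that this is one stray line in a synopsis set against a consistent procedure. Section 2.1 keeps the envelopes closed until the first visit, the visit table agrees, and staff holding envelopes for participants to draw could hardly follow the Summary by telephone. The Summary also never says that the group is disclosed on the call, and it lists written consents ahead of randomisation. Much of this stands. It makes the harmful course less likely and makes the bias conditional. It does not remove the contradiction, and it does not put the draw after consent within Visit 1.

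A reader might infer more in three ways, and the protocol does not support any of them.

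- **That selection by group is built into the plan.** It is not. It needs the Summary to be followed and the group to be disclosed early, and section 2.1 closes that route.
- **That the bias can be sized from the group size.** With 15 per group, one enrolled person weighs 1/15 = 6.7 percentage points. Someone who declines before consent is not in that denominator, so this figure does not measure the effect. Any assumed refusal rate would be invented.
- **That the draw must also wait until both baseline questionnaires are complete.** Acceptance and practicability are collected in the weekly follow-up and final questionnaires, when the group is necessarily known. Nothing shown says that the first-contact or vaccination forms measure acceptance of a test frequency. The envelope also carries the participant number, so a late draw could leave forms or samples without their identifier until then. The order of these steps is a working choice.

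**Conclusion.** The contradiction is certain: the Summary allocates at Visit 0, while section 2.1 and the visit schedule allocate at Visit 1. That the Summary's timing precedes consent follows from reading it with section 2.1; the Summary does not say so itself.

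The consequence is conditional. If the Summary were followed and the group made known before Visit 1, refusals related to the group would go uncounted, and acceptance of the more frequent schedules would tend to be overstated. That direction assumes that heavier schedules deter more people. The size cannot be given.

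The point should be fixed before recruitment, because allocation carried out in the wrong order cannot be repaired afterwards. It does not call the design into question: this is a pilot in 45 people with a descriptive analysis, and the detailed sections already point to Visit 1.

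**What to change.** Make three small changes to the text.

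1. Delete the randomisation sentence from Visit 0 in the Summary.
2. List randomisation under Visit 1 in the Summary, in line with section 2.1 and the visit schedule.
3. Add to section 2.1 that the participant draws and opens the envelope only after signing written consent, and counts as randomised from that moment.

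The cost is one deletion, one added item and one sentence. No visit, procedure or staff time is added. Drawing directly after consent also makes the participant number available for the samples and questionnaires at the same visit.

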## 1 Introduction

At the end of 2019, a new coronavirus SARS-CoV-2 (severe acute respiratory syndrome coronavirus type 2) appeared for the first time in China as a causative agent of pneumonia. In January 2020, the virus was identified by the Chinese authorities and reported to the WHO. Since then, the new coronavirus has been spreading worldwide. In March 2020, the outbreak was officially declared a pandemic by the WHO Secretary-General (1).

Coronaviruses cause mainly mild colds in humans, but can also cause severe pneumonia. SARS-CoV-2 causes the disease COVID-19. COVID-19 can manifest itself in many ways and not only in the lungs, but also in other organ systems, such as the nervous system, the gastrointestinal tract, the cardiovascular system or in the kidneys. In addition, a relatively wide range of dermatological manifestations has been described, but these are rare overall (0.2-1.2%). Some patients with severe SARS-CoV-2 infection develop a hyperinflammatory syndrome 8-15 days after the onset of the disease, which can lead to multiple organ failure and is associated with high mortality. Severe courses may also occur in persons without known previous disease and in younger patients. However, severe courses of the disease are observed much more frequently in certain groups of people. These so-called risk groups or vulnerable groups include above all older persons. 86% of those who died of COVID-19 in Germany were 70 years old or older (median age: 82 years) (2).

The proportion of people in need of care increases with age. According to the Federal Statistical Office, 4.13 million people in Germany were in need of care within the meaning of the Long-Term Care Insurance Act (SGB XI) at the end of 2019. Four out of five people in need of long-term care (80% or 3.31 million) were cared for at home. Of these, 2.33 million persons in need of long-term care were cared for mainly by relatives (3). As a rule, the family caregivers not only have close contact with the person to be cared for, but also frequently have other external contacts, for example through their professional activities, which poses a potential risk of infection and transmission to the person to be cared for.

In addition, new SARS-CoV-2 variants are also spreading in Germany, for which the effects cannot yet be assessed. Since mid-December 2020, the United Kingdom (UK) has been reporting the increasing spread of the SARS-CoV-2 lineage B.1.1.7 (VOC 202012/01; VOC: variant of concern), which is characterised by an unusually high number of mutations, particularly in the viral spike (S) protein, with the help of which the virus attaches to human cells. It is now assumed that this variant exhibits increased transmissibility, resulting in a higher number of replications (2).

Herd immunity to protect against COVID-19 can be achieved either through a high vaccination rate or through natural infection. Herd immunity through natural infection would require a large population group (more than half) to undergo the disease and produce antibodies. However, it is not yet clear whether everyone acquires full immunity after passing through infection and how long this lasts. This scenario would be associated with a high number of seriously ill patients and deaths and would not be ethically justifiable (4).

The only currently viable way to achieve sufficient herd immunity is vaccination. Currently, 3 vaccines are licensed in Germany. However, due to the high demand, these cannot yet be provided in sufficient quantities. According to the RKI, only 1.5% of the adult population in Saxony-Anhalt is currently fully immunised (2 vaccinations) (5). To make matters worse, according to the recommendation of the STIKO (Standing Committee on Vaccination at the Robert Koch Institute), the vector-based COVID-19 vaccine from AstraZeneca is currently only recommended for people aged 18 to 64 years, based on the data currently available. For these reasons, the RKI has defined priority risk groups to be vaccinated who have a particularly high vulnerability or exposure risk (level 1=highest priority). Since most family caregivers are most likely to be assigned to level 3 or a higher level in the STIKO's prioritisation list, they will only benefit from this protective measure with a time lag (6).

Important measures to contain the pandemic are adherence to the AHA-L rules (distance-handwashing-everyday-mask-ventilation), quarantine measures in case of infection or contact

SuRIP/B-FAST  
Study Protocol Version 1.0,  
15.02.2021

with an infected person and testing in case of suspected infection (7=testing criteria). PCR from nasopharyngeal swabs, throat swabs or combined nasopharyngeal swabs is still considered the gold standard for testing. The use of other sample materials, such as pharyngeal rinse water/ gargle water and saliva, is being discussed, as the collection of these materials is significantly better tolerated. However, there are significantly fewer empirical values for these materials. For saliva, some groups describe a lower clinical diagnostic sensitivity (8, 9), while other groups found comparable or, in the case of some studies, even higher sensitivity of PCR diagnostics compared to bilateral nasopharyngeal swabs (10, 11).

Antigen tests are increasingly used to relieve the burden of PCR diagnostics. The RKI's "National Test Strategy SARS-CoV-2" recommends that staff e.g. in care facilities and in outpatient care without a COVID-19 case in areas with an increased 7-day incidence (>50/100,000 inhabitants) should be regularly tested e.g. by means of antigen testing. For regular serial testing, the test regulation provides for an entitlement to testing once a week (12,13).

Due to a lack of studies and a possibly lower sensitivity, screening of asymptomatic individuals is currently discouraged, as test results only provide a snapshot. However, modelling and initial population-based studies suggest that the most important factors for effective surveillance are the frequency of testing and the speed with which a result is available, rather than the sensitivity of the testing system (14, 15 ,16).

